## Abstract

**Introduction:**

Ebola virus disease (EVD) continues to be a significant public health problem in sub-Saharan Africa, especially in the Democratic Republic of the Congo (DRC). Large-scale vaccination during outbreaks may reduce virus transmission. We established a large population-based clinical trial of a heterologous, two-dose prophylactic vaccine during an outbreak in eastern DRC to determine vaccine effectiveness.

**Methods and analysis:**

This open-label, non-randomised, population-based trial enrolled eligible adults and children aged 1 year and above. Participants were offered the two-dose candidate EVD vaccine regimen VAC52150 (Ad26.ZEBOV, Modified Vaccinia Ankara (MVA)-BN-Filo), with the doses being given 56 days apart. After vaccination, serious adverse events (SAEs) were passively recorded until 1 month post dose 2. 1000 safety subset participants were telephoned at 1 month post dose 2 to collect SAEs. 500 pregnancy subset participants were contacted to collect SAEs at D7 and D21 post dose 1 and at D7, 1 month, 3 months and 6 months post dose 2, unless delivery was before these time points. The first 100 infants born to these women were given a clinical examination 3 months post delivery. Due to COVID-19 and temporary suspension of dose 2 vaccinations, at least 50 paediatric and 50 adult participants were enrolled into an immunogenicity subset to examine immune responses following a delayed second dose. Samples collected predose 2 and at 21 days post dose 2 will be tested using the Ebola viruses glycoprotein Filovirus Animal Non-Clinical Group ELISA. For qualitative research, in-depth interviews and focus group discussions were being conducted with participants or parents/care providers of paediatric participants.

**Ethics and dissemination:**

Approved by Comité National d’Ethique et de la Santé du Ministère de la santé de RDC, Comité d'Ethique de l'Ecole de Santé Publique de l’Université de Kinshasa, the LSHTM Ethics Committee and the MSF Ethics Review Board. Findings will be presented to stakeholders and conferences. Study data will be made available for open access.

**Trial registration number:**

NCT04152486.

Strengths and limitations of this studyThis is the first large-scale trial designed to measure effectiveness of a two-dose Ebola vaccine through open label delivery to general populations in an Ebola-affected area.This is the first clinical trial to administer this vaccine regimen to pregnant women.The pragmatic design facilitated trial delivery during an active Ebola epidemic where the future location of new cases is uncertain.A test-negative case-control analysis to estimate vaccine effectiveness in a situation where a randomised controlled trial with a control arm was not possible.A non-randomised design is a limitation of this study.

## Introduction

### Background and rationale

Ebola virus disease (EVD) is caused by Ebola viruses (EBOV) and has a case fatality rate ranging from 30% to 90%.^1^ Bats are thought to be the reservoir, with human infection resulting from contact with excrement or saliva from bats or other intermediate animal hosts.^2–5^ Large outbreaks are fueled almost exclusively by subsequent human-to-human transmission.^2 6 7^

Vaccination is now a proven preventative measure for EVD control. During the 2013-2016 EVD outbreak in West Africa, a single dose of the rVSV-ZEBOV-GP vaccine (ERVEBO, Merck & Co.) given through a phase 3 cluster-randomised, ring-vaccination trial in Guinea showed 100% protective efficacy against EVD between day 10 and day 31 post randomisation.^8^ In 2016, the WHO Strategic Advisory Group of Experts on Immunization recommended the rapid deployment of rVSV-ZEBOV-GP for EVD outbreaks under an expanded access (compassionate use) protocol and the vaccine was licensed by the Democratic Republic of the Congo (DRC), Burundi, Ghana and Zambia in February 2020.^9 10^

Since the discovery of EBOV in 1976, the DRC has recorded 12 outbreaks. On 1 August 2018, the 10th EVD outbreak was declared in North Kivu Province.^11^ The outbreak progressively expanded across a large, highly populated area, characterised in recent years by civil unrest, armed militia groups, internally displaced persons and a substantial United Nations peacekeeping mission.^12^ The outbreak response focused on strategies that were previously adopted for the control of EVD outbreaks but was periodically hindered by attacks on Ebola Treatment Centres (ETCs) and on response workers. New cases continued to emerge in North Kivu and neighbouring provinces, prompting consideration of additional vaccine programmes that might assist in preventing the spread of this infection to unaffected communities. In early 2019, WHO conducted an evaluation of the suitability of candidate EVD vaccines for further clinical study and recommended several vaccines including VAC52150 (Ad26.ZEBOV, MVA-BN-Filo), a heterologous two-dose prophylactic vaccine manufactured by Janssen Vaccines and Prevention B.V.^13^

### Objectives

Following the WHO evaluation, we are conducting an open-label, non-randomised, population-based trial in North Kivu Province. This trial is named ‘Evaluation of a heterologous, two-dose preventive Ebola vaccine for effectiveness and safety in the Democratic Republic of the Congo’. The protocol number is DRC-EB-001. The primary objective is to estimate the vaccine effectiveness (VE) of Ad26.ZEBOV, Modified Vaccinia Ankara (MVA)-BN-Filo for prevention of EVD in adults and children aged 1 year or above. Secondary objectives are to: (1) assess the safety of Ad26.ZEBOV, MVA-BN-Filo, (2) estimate the coverage of dose 1 and dose 2 of Ad26.ZEBOV, MVA-BN-Filo overall and in different target groups (by gender, age and location) and (3) to explore the knowledge and perceptions of persons eligible for large-scale delivery of a preventative EVD vaccine with a two-dose vaccine strategy. An exploratory objective is assessing immunogenicity of Ad26.ZEBOV, MVA-BN-Filo in a subset of participants who received dose 2 outside the recommended interval between doses 1 and 2. This is the first study providing Ad26.ZEBOV, MVA-BN-Filo to pregnant women (table 1).

**Table 1 T1:** The WHO Trial Registration Data Set for the DRC-EB-001 trial

Data category	Information
Primary registry and trial identifying number	ClinicalTrials.gov NCT04152486
Date of registration in primary registry	5 November 2019
Source(s) of monetary or material support	Coalition for Epidemic Preparedness Innovations (CEPI), the Paul G. Allen Family Foundation, the UK Department for International Development (DFID) and Wellcome
Sponsor	London School of Hygiene & Tropical Medicine (LSHTM)
Sponsor contact and contact for public queries	[name] [contact]
Public title	Effectiveness and safety of a Heterologous, Two-dose Ebola Vaccine in the DRC
Scientific title	Evaluation of a heterologous, two-dose preventive Ebola vaccine for effectiveness and safety in the Democratic Republic of the Congo
Countries of recruitment	The Democratic Republic of the Congo
Health condition(s) studied	Ebola virus disease (EVD)
Intervention(s)	Ad26.ZEBOV, MVA-BN-Filo
Key inclusion criteria	Healthy volunteers Aged ≥1 year Both sexes (including pregnant and breastfeeding women)
Key exclusion criteria	Known EVD infection Having received any experimental EVD vaccines within 1 month
Study type	Interventional
Allocation	Open label, single arm
Primary purpose	Prevention
Phase	III
Date of first enrolment	14 November 2019
Target sample size	500 000
Recruitment status	Complete
Primary outcome(s)	To estimate the vaccine effectiveness of population-based vaccination delivery with the Ad26.ZEBOV, MVA-BN-Filo vaccine regimen for the prevention of EVD in adults and children aged 1 year or above. (timeframe: from 2 weeks after intervention to end of study)
Key secondary outcomes	To assess safety of the Ad26.ZEBOV, MVA-BN-Filo vaccine (timeframe: From dose 1 vaccination to 1 month post dose 2) To estimate the coverage of dose 1 and dose 2 of the Ad26.ZEBOV, MVA-BN-Filo vaccine regimen overall and in different target groups (timeframe: vaccination period) To explore the knowledge and perceptions of persons eligible for large-scale delivery of a preventative Ebola vaccine with a two-dose vaccine strategy (timeframe: vaccination period)
Other outcomes	To assess immunogenicity of the Ad26.ZEBOV, MVA-BN-Filo vaccine in a subset of participants who received dose 2 outside the recommended interval between dose 1 and dose 2.
Ethics review 1	Approved by LSHTM Research Ethics Committee Date of approval: 15 October 2019 Name and contact details: [name] [contact]
Ethics review 2	Approved by Médecins Sans Frontières Ethics Review Board Date of approval: 15 October 2019 Name and contact details: [name] [contact]
Ethics review 3	Approved by Comité d'éthique de l'école de santé publique, Université de Kinshasa Date of approval: 22 October 2019 Name and contact details: [name] [contact]
Ethics review 4	Approved by Comité national d’éthique et de la santé, Ministère de la Santé Publique, République Démocratique du Congo (RDC) Date of approval: 23 October 2019 Name and contact details: [name] [contact]

Ad26, Adenovirus serotype 26; EVD, Ebola virus disease; MVA, Modified Vaccinia Ankara.

## Methods

### The vaccine

The vaccination regimen comprised two vaccine candidates, both given as a 0.5 mL intramuscular injection in the upper section of the deltoid muscle or in the thigh in the case of young children:

Ad26.ZEBOV: a monovalent vaccine expressing the full-length glycoprotein (GP) from EBOV Mayinga, that is produced in the human cell line PER.C6, 5×10^10^ viral particles and given at day zero.MVA-mBN226B, or MVA-BN-Filo: a multivalent vaccine expressing the GP of EBOV (100% homologous with the GP expressed by Ad26.ZEBOV), Sudan and Marburg Musoke viruses; and the nucleoprotein of Taï Forest virus, 1×10^8^ infectious units given at day 56 (−14 day+28 day).

This regimen has been evaluated for immunogenicity and safety in 11 clinical trials in the UK, USA and East and West Africa, including previously EVD-affected countries.^14–21^ When administered in a 0, 56 day schedule in phase 2 and 3 studies, geometric mean concentrations of immunoglobulin G (IgG) binding antibody to the EBOV GP measured by the Filovirus Animal Non-Clinical Group (FANG) ELISA 21 days post dose-2 were 3810–11 790 EU/mL in healthy participants. The FANG ELISA assay has been validated for use in human sera.^22^ Unblinded safety data from 2390 adults showed only mild-to-moderate adverse events of short duration with no sequelae.^17^ No safety concerns were raised in HIV-infected individuals.^18^ In 649 children, the vaccine was highly immunogenic and had a similar safety profile as adults, with no Suspected Unexpected Serious Adverse Reactions.^19^ The European Commission granted marketing authorisation for Ad26.ZEBOV, MVA-BN-Filo on 1 July 2020.^20 21^

For this study, vaccine was donated by Janssen Vaccines and Prevention B.V. Vials were stored and shipped according to Good Manufacturing Practice guidelines with maintenance of the cold chain from Belgium to the vaccine depot in Goma, DRC and onto the vaccination clinics.

### Trial design

The protocol development team and investigators considered various trial designs that would allow estimation of vaccine efficacy or effectiveness in the context of an epidemic and vaccination activities with the rVSV-ZEBOV-GP vaccine. The value of placebo-controlled randomised controlled trial (RCT) designs was recognised but, given the ongoing EVD outbreak at the time of initiation of the study and taking into account sociocultural sensitivities and civil instability in the region, an RCT was not considered feasible or ethical. Rather, we adopted a test-negative case-control design, in which VE is estimated by comparing the history of vaccination in cases (test positives) compared with that in controls (test negatives), among individuals presenting with suspected EVD, with cases and controls defined retrospectively after EVD test results were confirmed. The test-negative design allows evaluation of VE in the general population without randomisation, and has been proposed as a valid approach for evaluation of EVD vaccines when RCTs are not feasible.^23 24^ The validity of this approach has been demonstrated by comparing results from test-negative case-control studies with those from randomised clinical trials of influenza and rotavirus vaccines. The two type of study yielded similar VE estimates.^25 26^

### Trial setting

This trial was planned to start in November 2019 and to end in February 2022. After discussion with local authorities, we initiated the trial in two administrative health areas in Goma, the provincial capital of North Kivu Province (population 634 197 in 2020). The choice of these locations was determined based on their potential risk for EVD transmission since there were strong ethnic, family and business links between these two health areas and the epidemic epicentres of Beni and Butembo, with frequent travel between the communities. Provincial administrative and health authorities provided data on the number of residents of these areas as well as the number of individuals working in health and community health settings. These people were provided with information about when and where vaccination would take place. We planned to subsequently move to health areas closer to the outbreak epicentre, guided by data on estimated risk of EVD, population density, security issues and transport links from Goma. However, plans to expand into new study sites were abandoned when the outbreak came under control and was declared over on 25 June 2020. As a consequence there was no possibility of acquiring VE data through the trial as the epidemic had not spread to the initial trial areas.

### Sample size

The required sample size for the primary effectiveness evaluation was 110 cases (test positives), to provide 80% power with alpha=0.05 for a two-sided test to demonstrate 70% VE under assumptions for coverage (percentage of vaccinated test negative individuals) ranging from 20% to 70% and ratio ranging from 1 to 4 test negatives per positive case (table 2).

**Table 2 T2:** Sample sizes for a test-negative case-control study design, assuming 80% power to detect an OR=1-VE, by per cent coverage among controls (those testing negative) and number of controls per case, with a two-sided alpha=0.05 test.

Vaccine efficacy (VE; %)	Coverage (% vaccinated among controls)	Sample size (no. of cases) by number of controls per case			
		1	2	3	4
90	5	210	171	157	149
	10	103	84	77	73
	20	50	40	37	35
	30	32	26	23	22
	50	19	15	13	12
	70	14	11	9	9
70	5	418	333	303	288
	10	211	167	152	144
	20	107	84	76	72
	30	74	57	52	49
	50	50	38	34	32
	70	46	34	30	28
50	5	962	749	677	641
	10	492	383	345	326
	20	260	201	181	171
	30	186	143	128	120
	50	137	103	92	86
	70	141	105	92	86
30	5	3070	2350	2109	1989
	10	1593	1218	1092	1029
	20	866	659	590	555
	30	638	483	432	406
	50	499	375	334	313
	70	553	412	364	340

This sample size also provides 80% power to demonstrate 90% VE under assumptions for coverage ranging from 10% to 70% and ratio of test positives to test negatives ranging from 1 to 4 test negatives to a test positive case. It will also provide 80% power to demonstrate 50% VE under assumptions for coverage ranging from 50% to 70% and ratio of test positives to test negatives ranging from 2 to 4 test negatives to a test positive case.

We estimated that vaccination of approximately 500 000 people with Ad26.ZEBOV, MVA-BN-Filo in transmission areas would achieve the sample size of 110 confirmed EVD cases under the following assumptions: (1) an EVD incidence of 4.1/10 000 in the absence of Ad26.ZEBOV/MVA-BN-Filo-induced immunity, corresponding to the median attack rate per health area after the first year of the epidemic in the DRC; and (2) 30% of confirmed cases had received the rVSV-ZEBOV-GP (in accordance with surveillance data) and would therefore be excluded from the effectiveness analysis. We assumed a homogeneous attack rate, while recognising that it could vary according to the location of vaccine deployment and the evolution of the epidemic.

After the VE analysis had been conducted based on 110 cases, the study team planned discussions to review the findings and the value of continuing to enrol participants.

Two subsets of individuals, 1000 vaccinated individuals (500 adults and 500 children) and 500 pregnant participants (250 pregnant predose 1 and 250 pregnant within 30 days of dose 2), were enrolled for more active follow-up for safety reporting (table 3). The sample size allowed for 95% probability to detect at least one vaccine related serious adverse event (SAE) if the true incidence of that SAE is at least 1.2% with 250 individuals, 0.6% with 500 individuals, or 0.3% with 1000 individuals.

**Table 3 T3:** Time and event schedule for intervention delivery and safety evaluations

Preparation	Up to 1 month before study starts	D0 Dose 1 visit	D7 (−3/ +7 day)	D21 (−6/ +7 day)	D56 Dose 2 visit (−14/+28 day)	D7 post dose 2 (−3/ +7 day)	D21 post dose 2 (−3/+7 day)	1 month post dose 2 (−7 day/+1 month)	3 months post dose 2 (±14 day)	6 months post dose 2 (−14/+28 day)	3 months post delivery
Mapping and selection of study sites	X										
Community engagement and social mobilisation	X										
Consent, vaccination dose 1		X									
Vaccination dose 2					X*						
SAE assessment					X**†**			X‡			
Safety subset					X			X§			
All pregnant women					X**¶**			X			X**
Pregnancy subset		X	X††	X††	X	X††		X††	X††	X††	X‡‡
Immunogenicity subset					X§§		X§§				

*Dose 2 may be given between D42 and D84. Participants who return for dose 2 after 84 days will still be vaccinated.

†D56 safety data are collected at dose 2 visits.

‡Passive serious adverse event (SAE) recording from main study participants through participant-initiated phone calls or other contact with team, until 1 month post dose 2.

§Safety subset: 1000 participants will be actively followed up for SAEs by phone at 1 month post dose 2.

¶If study vaccinations have been paused, all pregnant participants who have not received dose 2 will be called at D56 (±7 days) to collect safety data.

**All pregnant women will have their birth outcomes collected around 3 months post delivery (between 1 and 3 months). When feasible, team to visit if the woman is not contactable by telephone.

††Pregnancy subset: safety telephone calls to collect SAEs at D7 and D21 post dose 1, and then at D7, 1 month, 3 months and 6 months post dose 2, unless delivery is before these time points.

‡‡100 infants born to women in the pregnancy subset will be given a full clinical examination around 3 months after delivery (between 1 and 6 months).

§§Immunogenicity subset: a subset of paediatric and adult participants will have a venous blood draw at the dose 2 visit before vaccination. A second blood sample will be taken 21 days (−3/+7 day) after their dose 2 vaccination. Enrolment of this subset will continue until at least 50 adults and 50 children have had blood samples collected for immunogenicity at dose 2 and 21 days post dose 2.

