### Safety measurements

Following each vaccination, we gave participants instructions to contact the study team for any SAEs occurring up to 1 month post dose 2 and where to seek care for medical problems, including antenatal care for pregnant women (table 3). Whenever possible, we documented the diagnosis or syndrome related to SAEs, rather than multiple symptoms. Investigators then assessed any potential causal relationship to vaccination. We followed up SAEs to resolution or stabilisation, irrespective of severity or whether considered vaccine related. We allowed unscheduled study follow-up visits on adverse events at the investigator’s discretion.

Follow-up of pregnant women is ongoing. We compiled a registry of pregnant women and we encouraged women who become pregnant within 1 month of any vaccine dose to contact the team. We are telephoning all known pregnant women 1–3 months after delivery to record birth outcomes or, when possible, a study clinician visits them in person if they are not contactable by telephone. In the pregnancy subset, we actively follow by telephone 250 women who were pregnant at the time of dose 1 and up to 250 who became pregnant within 30 days (1 month) of administration of either dose 1 or 2. We make calls to collect SAE data at D7 (−3/+7 day) and D21 (−6/+7 day) post dose 1, D7 (−3/+7 day) post dose 2, and at 1 month (−7 day/+1 month), 3 months (±14 day) and 6 months (−14/+28 day) post dose 2 (unless delivery occurs before these time points). We are performing a clinical examination on the first 100 infants born to women in the pregnancy subset at around 3 months of age (ranging from 1 to 6 months). We offer a small bag of rice, cassava or equivalent to mothers returning to the clinic for infant safety follow-up visits.

In the safety subset, we actively followed the first 500 adults and first 500 children enrolled by telephone 1 month (−7 days/+1 month) after administration of dose 2.

For acute medical problems, we provide care to participants with referral to health clinic and hospitals as necessary. The trial sponsor and funder have put in place global and local clinical trial insurance covers to compensate any potential harm to participants.

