## Outcomes

The primary study outcomes are:

1) The numbers and odds of vaccination status in EVD cases and in EVD-negative controls in a test-negative case-control study with a target sample size of 110 laboratory confirmed EVD cases matched to controls who test negative for EVD. Effectiveness is derived from the OR for vaccination in cases compared with controls to calculate VE.

The secondary outcomes include:

The number and proportion of adults and children with solicited and unsolicited SAEs from the date of first vaccination to 1 month post dose 2. Data on SAEs within 1 month post dose 2 that are considered related to vaccination with Ad26.ZEBOV, MVA-BN-Filo in adults and children.The number and proportion of adults and children receiving dose 1.The number and proportion of adults and children receiving dose 2.The number of participants participating in in-depth interviews and focus group discussions on participant and community perceptions of the trial and on vaccine acceptability.

The exploratory outcome includes:

The level of IgG antibodies against EBOV GP in samples collected from participants in the immunogenicity subset who received dose 2 outside the recommended interval between dose 1 and dose 2.

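### Pregnancy-subset SAE calls stop at delivery while the SAE window is still open, so maternal SAEs around and after delivery are not actively solicited and are likely under-ascertained

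*Protocol article*

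**What the plan says.** The stop rule is in Table 3 footnote ††: after the two post dose 1 calls, the subset is called "and then at D7, 1 month, 3 months and 6 months post dose 2, unless delivery is before these time points". The Abstract, the subset description under Intervention delivery and the Safety measurements section repeat it, the last with "and 6 months (−14/+28 day) post dose 2 (unless delivery occurs before these time points". It is not a one-off slip of wording.

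The Outcomes section defines the safety outcome as the "number and proportion of adults and children with solicited and unsolicited SAEs from the date of first vaccination to 1 month post dose 2". Delivery does not shorten that window.

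Other routes for SAE data are:
- Passive reporting. Table 3 footnote ‡ gives "Passive serious adverse event (SAE) recording from main study participants through participant-initiated phone calls" or other contact with the team, and Safety measurements says "we gave participants instructions to contact the study team for any SAEs occurring up to 1 month post dose 2". Neither stops at delivery.
- The dose 2 visit: "D56 safety data are collected at dose 2 visits" (footnote †). If vaccination is paused, pregnant participants without dose 2 are called at about D56 (footnote ¶).
- A contact after delivery: "We are telephoning all known pregnant women 1–3 months after delivery to record birth outcomes". Maternal SAEs are not named among its contents.
- A mark at 1 month post dose 2 in the Table 3 row for all pregnant women. As reproduced, it has no footnote and no delivery exception, and the text describes no matching call.

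The Safety analysis section will summarise SAE incidence by whether vaccination was received in pregnancy.

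**The concern.** Each call covers the time since the previous contact. If the next call is cancelled because the woman has delivered, no later subset SAE call covers the interval containing labour, delivery and the early postpartum. Delivery can follow from an SAE or be accompanied by one (preterm labour, emergency delivery), so the stop is informative. A woman who delivers before dose 2 and then receives it gets no subset call at all after that dose, whereas a member of the general safety subset is called at 1 month.

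The article describes this as the first study to give the regimen to pregnant women, and it created the subset to follow them more actively than passive reporting allows. What is at stake is how complete the maternal SAE count is, and how far the stated detection limit for 250 women can be relied on near the end of the window.

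**Working it through.** **1. The plan's own figure.** The Sample size section states a 95% probability of at least one related SAE at a true incidence of 1.2% (n=250), 0.6% (n=500) or 0.3% (n=1000). With P = 1 − (1 − p)^n, the probabilities are 95.1%, 95.1% and 95.0%. The 95% limit, 1 − 0.05^(1/n), is 1.19%, 0.60% and 0.30%. The figures reproduce, on the premise that every woman is observed.

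**2. Which calls matter.** The outcome closes at 1 month post dose 2. Only the D7 and D21 post dose 1 calls and the D7 and 1-month post dose 2 calls fall inside it. The 3- and 6-month calls do not bear on this outcome.

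**3. Which women.** At an on-time dose 2, a woman who conceived up to 30 days before that dose is at most about 30 + 30 = 60 days from conception at the 1-month call. If she conceived up to 30 days before dose 1, the figure is about 30 + 56 + 30 = 116 days. Both are far from term, so the affected group is essentially the 250 pregnant at dose 1.

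**4. Share delivering before the call.** From the documents: dose 2 at D56, allowed window D42 to D84, later doses still given. Assumed, because the documents give no gestational ages: gestation at dose 1 uniform over 4–38 or 4–28 weeks; birth at mean 39.3 weeks (275.1 days), SD 12 days; 1 month = 30 days; women still pregnant at dose 1.

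For dose 2 at D56 the call falls on day 86. Ignoring the spread in birth date:
- 4–38 weeks: (266 − (275.1 − 86)) / (266 − 28) = 76.9/238 = 32%.
- 4–28 weeks: (196 − (275.1 − 86)) / (196 − 28) = 6.9/168 = 4%, or 5% once the spread is included.

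With the spread included, by simulation:

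| Gestation at dose 1 | Dose 2 | Deliver before dose 2 | Deliver before 1-month call | Between the two |
|---|---|---|---|---|
| 4–38 wk | D56 | 19% | 32% | 13% |
| 4–38 wk | D84 | 31% | 44% | 13% |
| 4–38 wk | ~D214 | 86% | 97% | 11% |
| 4–28 wk | D56 | 0% | 5% | 5% |
| 4–28 wk | D84 | 5% | 21% | 16% |
| 4–28 wk | ~D214 | 80% | 96% | 16% |

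The D214 rows reflect the suspension from 10 April to 14 September 2020. A woman whose D56 fell on 10 April had dose 1 on 14 February, and 14 September is 213 days later.

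Sensitivity: gestation uniform from 12 to 40 weeks with birth fixed at 280 days gives 86/(280 − 84) = 44% at D56. The share depends heavily on the gestation assumed.

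**5. Effect at the 1-month call, dose 2 at D56.**
- 32%: 250 × 0.32 = 80 not called, 170 called. Limit 1 − 0.05^(1/170) = 1.7%. Probability of at least one SAE at 1.2% incidence = 1 − 0.988^170 = 87%.
- 5%: about 13 not called, 237 called. Limit 1.3%, probability 94%.

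This is the limit at that call, not over the whole window, because women not called at 1 month still contribute earlier active contacts.

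**The case against.** The strongest objection is that ascertainment does not cease at delivery, and this stands. Passive reporting stays open to 1 month post dose 2, and the dose 2 visit collects safety data from anyone who attends. Of the 32% above, 19 points deliver before D56. If those women attend for dose 2, that visit can cover delivery and the early postpartum, which leaves about 13%, or 5% under the earlier-gestation assumption. That is about 13 to 32 women, or 3–6% of the full subset of 500. It does not restore a call after dose 2 for the women who delivered before it.

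A reader might infer that maternal SAEs after delivery are missed altogether. The documents do not support that, because the passive and visit-based routes have no delivery exception. A reader might also infer that the 3- and 6-month calls are largely empty and weaken the outcome. Those calls lie outside the SAE window, and the women who conceived around the doses would mostly still be pregnant at them.

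It is also fair to say that the post-delivery contact may ask about maternal events in the full protocol, which is not shown. The article names birth outcomes only, so the point rests on the stated stop rule and not on that silence. The 1-month mark for all pregnant women may likewise be an active SAE contact. If it is, it conflicts with footnote ††, and the two need reconciling.

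Finally, dose 2 delivery ended on 9 February 2021, so many of the calls can no longer be made. That limits the remedy but not the point.

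**Conclusion.** The point holds as under-ascertainment. By a rule stated consistently in the article, active SAE follow-up in the pregnancy subset ends at delivery while the outcome window may still be open, and the stopping event is related to the outcome. The likely direction is downward for maternal SAEs around and after delivery, relative to the active follow-up the subset was meant to provide. It does not show that pregnant women are followed less than the main cohort, most of whom have passive reporting only.

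With dose 2 at D56, about 5–32% of the women pregnant at dose 1 would lose the 1-month call, of whom about 5–13 percentage points deliver between dose 2 and that call. The shares rise with later dose 2, to 21–44% at D84 and nearly all at about D214. At 32%, the 1.2% limit becomes about 1.7% at that call. All of this rests on assumed gestational ages, and the trial's own records would replace those assumptions. The issue deserves correction and transparent reporting, but it does not undermine the safety evaluation as a whole.

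**What to change.** 1. Make the D7 and 1-month post dose 2 SAE calls whether or not the woman has delivered, wherever those call windows are still open.
2. At the existing contact 1–3 months after delivery, ask about maternal SAEs since the last contact, with dates. Count in the SAE outcome only events dated inside the window to 1 month post dose 2.
3. Reconcile footnote †† with the 1-month mark in the Table 3 row for all pregnant women: state what that mark is, and whether it applies after delivery.
4. Report actively and passively ascertained SAEs separately for the pregnancy subset, with the number of women whose calls ended at delivery and the timing of delivery relative to dose 2.

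The cost is one set of questions added to a contact already made, up to about 80 extra calls per post dose 2 time point under the larger D56 assumption (more if dose 2 was late), and one table. No vaccination or clinical care changes. Timing limits items 1 and 2. Under the same assumptions, a woman 4 weeks pregnant at the last dose 1 date (29 February 2020) delivers around early November 2020, and her post-delivery contact is due by about early February 2021. For women already past that contact, a single retrospective call is the only way to recover events. Otherwise item 4 and a stated limitation are what remain.
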